**Methods:**

We aim to recruit a minimum of 90 patients—30 patients for SBT, 30 patients for ABT, and 30 patients with no blood transfusion. SBT and ABT form the 2 experimental arms, whereas no blood transfusion forms the control cohort. Available patient data will be reviewed to determine tumor burden secondary to metastasis and postoperative survival and disease progression, improvement in pain, and neurological and ambulatory status. Data collected will be studied postoperatively at 3, 6, 12, 24, 36, and 48 months or until demise, whichever occurs first. Outcomes of the experimental groups will be compared with those of the control group. Outcomes will be analyzed using 1-way ANOVA and Fisher exact test. The Kaplan-Meier curve and a log-rank test will be used to study overall survival. A multivariate and competing risk analysis will be used to study the association between blood transfusion type and tumor progression. All statistical analyses will be done using Stata Special Edition 14.0 (StataCorp LP).

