## Methods

### Recruitment

This study aims to recruit a minimum of 90 patients of whom 30 will receive SBT (with or with no allogeneic blood), 30 will undergo ABT, and the remaining 30 will have NBT. From our experience of treating patients with tumor, there are likely to be very few patients who receive only SBT. The majority of patients receiving SBT are likely to receive both SBT and ABT in various proportions. SBT and ABT form the 2 experimental arms, whereas patients with NBT form the control cohort. We will compare the number of patients receiving only SBT with those receiving ABT, if the sample sizes are sufficient.

Patients will be selected from specialist outpatient spine clinics or inpatient wards. These patients may be referred from an inpatient medical oncology team for management, especially in the setting of MSD with cord compression resulting in symptoms such as pain or neurology. A thorough examination of clinical history, physical examination, and review of imaging will be done, and appropriate patient management options will be discussed by the attending orthopedic surgeon. During the enrollment period, whenever a spine surgeon has obtained surgical consent for MSTS in patients with MSD, the principal investigator (NK) will be informed either by a telephone call or by text messaging.

The *research assistant* who is on-site at the National University Hospital during office hours or any member of the research team who is available will interview the patient. During this interview, the interviewer will confirm whether the inclusion criteria are fully met. The study will be explained to suitable subjects, including the advantages as well as possible intra- and postoperative risks of the reinfusion of salvaged blood. A copy of the *patient information sheet and consent form* will be provided to the patient, detailing the recruitment procedures, our objectives, hypotheses, and background information, and any queries will be addressed. Subsequently, written informed consent will be obtained from the patient.

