Blood transfusion details will be collected from anesthetists immediately after the operation. Depending on the type of blood transfusion done during the surgery, that is, ABT only or SBT with or with no ABT or NBT, the patient will be categorized into the appropriate study cohort. All patients undergoing MSTS will receive tranexamic acid as an intravenous bolus before induction of anesthesia as per the department protocol, with subsequent top-up dosages every 4 hours during MSTS. If excessive blood loss is expected during surgery, such as in a separation surgery, continuous infusion of tranexamic acid is given to the patient.

Postoperatively, all subjects will be followed up individually by their operating surgeons, as per the standard of care at the National University Hospital. No additional patient follow-up sessions by the research team will be required. Clinical data and patient outcomes will be accessed via the computerized patient support system and EPIC system at monthly intervals. All available radiological data and clinical notes from the patients’ follow-up by their treating surgeons or physicians will be reviewed by the research team. This is to determine the postoperative outcomes such as survival and disease progression. The collected data will be analyzed postoperatively at 3, 6, 12, 24, 36, and 48 months. The data collection and follow-up of available records will continue over a period of 4 years postoperatively or until the patient’s demise, whichever occurs first. The collected outcomes of the 2 experimental groups (patients who received SBT with or without ABT) will be compared with those of the control group (patients who received NBT) as well as with the available historical data from the literature.

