### Statistical Analysis

We have defined *disease progression* as the increase in the size of an existing metastatic lesion or the appearance of a new lesion in the lung, liver, or the spinal column, which can be visualized by using radiological imaging.

Demographic and clinical characteristics of patients will be summarized using mean (SD) values for continuous variables with approximately normal distribution, median (IQR) values for continuous variables with skewed distribution, and frequency (percentage) for categorical variables. A 1-way ANOVA will be used to compare the mean of a normally distributed variable across the 3 blood transfusion groups, whereas a Kruskal-Wallis rank test will be used for the comparison of medians. A Fisher exact test will be implemented for categorical variables accounting for potential small frequencies.

The association between individual characteristics and OS will be studied by using the Kaplan-Meier curve and a log-rank test. The crude hazard ratio and its 95% CI will be used to measure the association between individual characteristics and OS and will be calculated based on their original definitions. Multivariate Cox proportional hazard regression will then be used to adjust for statistically significant confounders for the relationship between the type of blood transfusion and OS. The proportional hazards assumption will be tested after the final model is obtained.

The association between the type of blood transfusion and tumor progression will be investigated by the competing risks analysis, taking death without tumor progression as the competing event. First, cumulative incidence curves of the 3 blood transfusion groups will be plotted nonparametrically, and then we will model the relation via a subdistribution hazard regression model. The measure of association will be quantified by the crude subdistribution hazard ratio; its 95% CI and *P* value will be analyzed in a univariate analysis. Subsequently, a multivariate analysis will be used to adjust for potential confounders. All statistical analyses will be done using Stata Special Edition 14.0 (StataCorp LP). The statistical tests will be assumed to be 2-sided, with the conventional 5% significance level.

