#### Analysis of Primary Outcome Measures

We intend to compare the proportion of patients with MSTS requiring blood transfusion and the amount of ABT required. The primary analysis will be based on the intention-to-treat principle. A Fisher exact test will be used to compare the 2 arms. The exact 95% CI will also be calculated for the difference in the ABT rate between the 2 arms.

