### Limitations

The limitation of this study is that not all patients undergoing MSTS will survive for the total follow-up period of 4 years, thereby theoretically leading to potential underreporting of disease progression. The sheer number of possible primary tumors in MSD also inevitably leads to heterogeneity, which can be overcome through propensity score–matching analysis.

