### Broader Implications

Through the reporting of our analysis, this study will help reduce the use of ABT, reduce the burden on blood banks, and improve the overall blood management of patients with MSTS. This improvement in blood management will prevail even with the improvement of surgical techniques in the management of MSTS, that is, introduction of minimally invasive surgery techniques and the regular use of navigation. This is because the 2 techniques mentioned earlier will reduce blood loss during the steps of spinal instrumentation but are unlikely to have any effect on blood loss while performing decompression. Decompression and separation surgery presently still form a major component of MSTS and will continue to do so, resulting in significant bleeding that requires replenishment potentially in the form of SBT.

In this protocol, we have proposed a prospective observational nonrandomized study design as the ethical appropriateness of blinding or randomizing these patients is a key concern in our region and country. Blinding or randomization of patients with MSD could be deemed unethical, especially among patients who may not agree to receive SBT or ABT as this will limit the blood transfusion type applicable for them. This could be attributed to the current lack of clinical evidence that SBT does not lead to disease progression or shortened survival among patients undergoing MSTS who receive SBT. With this research proposal, we aim to highlight the safety profile of SBT, together with a design protocol applicable for use in patients with MSD. Future research, such as propensity-matched studies, can be done to further validate the outcomes from our current protocol.

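### The overall-survival model adjusts only for confounders that pass a 5% significance screen, so real confounders of moderate strength can be left out of a non-randomised comparison

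*Protocol article*

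**What the plan says.** - **Design.** Under Broader Implications the authors write that "we have proposed a prospective observational nonrandomized study design". Under Recruitment, cohorts are assigned after the operation: "Depending on the type of blood transfusion done during the surgery", each patient is placed in the allogeneic (ABT), SBT or no-transfusion (NBT) cohort.
- **Size.** "This study aims to recruit a minimum of 90 patients of whom 30 will receive SBT", with 30 ABT and 30 NBT patients making up the rest. The Results section reports 140 recruited.
- **OS.** Statistical Analysis relates individual characteristics to OS by log-rank test and crude hazard ratio, at a two-sided 5% level. Then: "Multivariate Cox proportional hazard regression will then be used to adjust for statistically significant confounders".
- **Tumor progression.** The subdistribution hazard model in the same section is adjusted for potential confounders. Significance is not mentioned.
- **Other outcomes.** The abstract says "Outcomes will be analyzed using 1-way ANOVA and Fisher exact test", and Statistical Analysis adds Kruskal-Wallis for skewed variables. For the ABT rate, Analysis of Primary Outcome Measures says "A Fisher exact test will be used to compare the 2 arms". None of these tests carries covariates.
- **Propensity score.** Limitations says that the variety of primary tumors "inevitably leads to heterogeneity, which can be overcome through propensity score" matching. Broader Implications says "Future research, such as propensity-matched studies, can be done to further validate the outcomes".

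**The concern.** Confounding depends on how a factor relates to both the transfusion received and the outcome. Whether its p-value against OS falls below 0.05 in one small sample is a different question. Here cohort membership follows bleeding, extent of surgery and consent to SBT, and the article itself concedes heterogeneity of primary tumors. A factor that is truly prognostic and unevenly spread over the cohorts can fail the screen for lack of power, and its imbalance then stays in the SBT hazard ratio.

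The first hypothesis is that SBT does not increase the risk of progression or worsen OS. Residual confounding could create a false safety signal or hide a real one, depending on which cohort has the worse prognosis, and the documents do not tell us that. The two outcomes of the primary objective also follow different adjustment rules without a reason given.

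The third hypothesis expects fewer complications and a shorter stay with SBT than with ABT. An unadjusted difference between cohorts formed by the transfusion received gives weak support for that.

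**Working it through.** The article gives no effect size, event count or power behind the minimum of 90, so there is no planned figure to reproduce. The calculation below is an illustration under stated assumptions.

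**Inputs from the article:** two-sided 5% level; 30 per group and 90 in total; 140 recruited; follow-up to 48 months or death.

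**Assumed:** exponential survival with median 10 months at the reference level; no drop-out; one binary factor with HR 1.5, present in 25% of one group, 50% of the other and 37.5% of the third; true SBT HR 1.00; 140 patients split into near-equal thirds; *significant* read as p < 0.05 in the univariate screen that precedes the Cox model.

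**Step 1: deaths.** Survival at 48 months is 2^(−4.8) = 0.036 without the factor and 2^(−7.2) = 0.007 with it. The proportion dying is 0.625 × 0.964 + 0.375 × 0.993 = 0.975. That gives 58.5, 87.8 and 136.5 deaths for 60, 90 and 140 patients.

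**Step 2: chance that the screen keeps the factor.** Power = Φ(ln HR × √(D·p(1−p)) − 1.96), with ln 1.5 = 0.4055 and p(1−p) = 0.375 × 0.625 = 0.234.
- 60 patients: 0.4055 × √13.7 = 1.50, and Φ(−0.46) = 0.32
- 90 patients: 0.4055 × √20.6 = 1.84, and Φ(−0.12) = 0.45
- 140 patients: 0.4055 × √32.0 = 2.29, and Φ(0.33) = 0.63

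**Step 3: distortion with no adjustment at all.** (1 + 0.5 × 0.5)/(1 + 0.5 × 0.25) = 1.25/1.125 = 1.11.

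**Step 4: what the stated rule does.** Cox simulation, 1,000 studies per row, factor HR 1.5:

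| Patients | Factor kept | Crude HR, all studies | Crude HR where factor dropped | HR under the screening rule | HR, factor always entered | 95% CI coverage, screened / always entered |
|---|---|---|---|---|---|---|
| 60 (two groups) | 32% | 1.11 | 1.06 | 1.05 | 1.00 | 93.9% / 93.0% |
| 90 (three groups) | 45% | 1.10 | 1.05 | 1.04 | 1.00 | 93.6% / 93.6% |
| 140 (three groups) | 65% | 1.11 | 1.06 | 1.02 | 1.00 | 94.4% / 94.6% |

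A separate run of the 90-patient setting kept the factor in 44% of studies. With factor HR 1.8, the factor is kept in 57% of studies of 60 and 76% of studies of 90, with screened HRs of 1.04 and 1.02.

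**Step 5: several factors.** If three independent factors of this kind all acted in the same direction, the screened bias would multiply to between 1.02³ = 1.06 and 1.05³ = 1.16. Factors acting in opposite directions would partly cancel.

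**The case against.** The strongest reply is that the bias is small. A factor that fails the screen tends to be one that distorts little in that sample, which is why the HR in studies that drop it is about 1.05 to 1.06 and not 1.11. Strong factors mostly pass, and at 140 patients the average bias from one moderate factor is about 2%. This stands, and it limits the size of the point. It does not defend the rule, which gains nothing over entering the same factors regardless.

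A reader might infer more than the documents support:

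- **That the SBT hazard ratio would be off by 1.11, or by 1.11³ = 1.37 with three factors.** Those figures describe no adjustment at all, in every study. The plan does adjust.
- **That screening makes the confidence interval too narrow.** In the simulation, coverage was about the same with and without the screen.
- **That progression has the same flaw.** Its model has no significance filter as worded. The fault there is only the inconsistency.
- **That the amount of ABT has no usable test.** The Fisher test is tied to the ABT rate, and Kruskal-Wallis under Statistical Analysis can cover the amount.
- **That covariate adjustment would repair the ABT comparison.** Everyone in the ABT cohort has ABT and no one in the NBT cohort does, by definition. That is a separate problem.
- **That the two propensity statements contradict each other.** Limitations says matching can help, and Broader Implications suggests it for later studies. Both can be true. It is only unclear whether this study will do it.

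For complications and stay, a condensed article may leave adjusted models to a plan not shown. That part is weaker than the OS point, where a poor rule is actually written down.

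**Conclusion.** The concern holds for the OS model. The article fixes a significance-based covariate rule in a non-randomised study, and the rule differs from the one for progression in the same section. Under the assumptions above, a confounder with HR 1.5 is dropped in about two thirds of studies with 60 patients, somewhat over half with 90 and about a third with 140. The resulting bias in the SBT hazard ratio averages 2% to 5% per factor, in a direction that the documents do not determine. It is modest singly and can accumulate. These figures depend on the assumed factor strength, imbalance and near-complete mortality by 48 months; fewer deaths would make the screen weaker.

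For complications and length of stay, the only tests stated are unadjusted, so on the stated tests the hypothesised advantage over ABT would rest on crude comparisons. This is an inexpensive improvement worth making, and not a flaw that by itself invalidates the study.

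**What to change.** 1. In Statistical Analysis, replace the significance rule with a short prespecified covariate set chosen on prognostic grounds and sized to the expected number of deaths. Examples are primary tumor prognosis group, visceral metastasis, and preoperative performance or ambulatory status. Enter it whatever the p-values.
2. Use the same set for OS, tumor progression, complications and length of stay, by regression or by propensity (overlap) weighting if parameters must be spared.
3. Treat blood loss or extent of surgery as a sensitivity covariate, after checking overlap between cohorts, because it partly determines the transfusion given.
4. Do not fit a logistic model of any ABT on cohort. The cohort definition fixes the outcome in the ABT and NBT groups, so the cohort contrast has no finite estimate.
5. State under Limitations whether a propensity analysis belongs to this study or, as Broader Implications has it, to future research.

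The cost is plan wording, slightly wider confidence intervals and a few more models on data already collected. No change to recruitment or follow-up is needed.

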### Hypothesis

The working hypotheses of this study are as follows:

Reinfusion of IOCS-LDF–processed blood of patients undergoing MSTS does not increase the risk of disease progression, in terms of tumor progression (increase in size of existing metastatic lesions with or without the appearance of new metastasis) and OS.Patients receiving IOCS-LDF blood transfusion require less ABT.Patients receiving IOCS-LDF blood transfusion will experience fewer overall complications and shorter length of stay than patients receiving ABT.

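### The subdistribution hazard ratio is the only regression measure for tumor progression, so earlier death without progression in SBT patients could attenuate, hide or reverse a true increase in the progression rate

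*Protocol article*

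**What the plan says.** The Statistical Analysis section of the protocol article sets up a competing risks analysis of tumor progression, "taking death without tumor progression as the competing event". It has two steps. First, "cumulative incidence curves of the 3 blood transfusion groups will be plotted nonparametrically". Then a regression: "we will model the relation via a subdistribution hazard regression model". The effect measure is fixed as well: "The measure of association will be quantified by the crude subdistribution hazard ratio", with a multivariate analysis to follow. No cause-specific hazard model is named, either for progression or for death without progression.

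The hypothesis this serves is that reinfusing processed salvaged blood "does not increase the risk of disease progression, in terms of tumor progression" and overall survival (OS). OS has its own analysis by Kaplan-Meier, log-rank test and Cox regression: "Multivariate Cox proportional hazard regression will then be used to adjust for statistically significant confounders". The Limitations section notes that "not all patients undergoing MSTS will survive for the total follow-up period of 4 years", "thereby theoretically leading to potential underreporting of disease progression".

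**The concern.** The Introduction, Objectives and Discussion ask whether reinfused blood promotes tumor spread. That is a question about the rate of progression among patients who are alive and progression-free, which is the cause-specific hazard. The subdistribution hazard instead keeps patients who died without progression in the risk set. Higher mortality in one group therefore lowers that group's progression HR, even if salvaged blood does nothing to the tumor or makes it progress faster.

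Different mortality between groups is plausible on the article's own account. Allocation is nonrandomized, and the cohort is set by what was transfused during surgery. The Recruitment section expects most SBT patients to receive allogeneic blood too, and the Introduction links allogeneic transfusion to survival duration. The control cohort receives no blood at all. Under a hypothesis of no increase, a ratio pulled down by excess death errs toward a conclusion of safety.

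**Working it through.** **Inputs from the article.** Follow-up is 48 months or until death. The minimum is 30 patients per group. Tests are two-sided at 5%. Death without progression is the competing event. The article gives no progression rate, death rate or effect size, so there is no stated figure to reproduce and every rate below is an assumption.

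**Model.** Constant monthly hazards in group g: p_g for progression and d_g for death without progression. There is no other censoring before month 48.

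- Cumulative incidence of progression: F_g(t) = p_g/(p_g + d_g) × [1 − exp(−(p_g + d_g)t)], with density f_g(t) = p_g exp(−(p_g + d_g)t).
- Large-sample subdistribution HR for SBT (group 1) against comparator (group 0), equal group sizes: with r_g(t) = 1 − F_g(t), solve ∫ from 0 to 48 of { f_1 − (f_0 + f_1) × r_1e^b/(r_1e^b + r_0) } dt = 0. The HR is e^b. Proportionality does not hold exactly here, so this is an average over follow-up.

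**One setting in full.** Comparator 0.04/0.04 (progression/death per month), SBT progression HR 1.3 and death HR 1.6, so SBT hazards are 0.052/0.064.

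- Comparator at 48 months: 0.5 × (1 − e^−3.84) = 48.9%.
- SBT at 48 months: 0.052/0.116 × (1 − e^−5.568) = 44.7%.
- Subdistribution HR over 48 months: 0.93, although the progression rate is 30% higher with SBT.

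**Range.**

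| Comparator hazards (progression/death) | True progression HR | Death-without-progression HR | Subdistribution HR |
|---|---|---|---|
| 0.05/0.05 | 1.3 | 1.0 | 1.23 |
| 0.04/0.01 | 1.3 | 1.6 | 1.10 |
| 0.05/0.01 | 1.3 | 2.0 | 1.02 |
| 0.05/0.03 | 1.3 | 1.5 | 1.01 |
| 0.04/0.04 | 1.3 | 1.6 | 0.93 |
| 0.05/0.05 | 1.3 | 2.0 | 0.79 |
| 0.04/0.04 | 1.0 | 1.5 | 0.78 |

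**Simulation check.** With 200,000 patients per group at 0.05/0.05, progression HR 1.3 and death HR 2.0, a cause-specific Cox model gives 1.30 and the subdistribution model gives 0.79 on the same data. The 48-month progression incidence there is 39.4% with SBT against 49.6%, so by month 48 the curves are reversed too.

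**How far OS would warn.** Power for a two-group comparison with D deaths is Φ(√(D/4) × ln HR − 1.96).

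- With 30 against 30 and all 60 patients dead: √15 × ln 1.5 − 1.96 = −0.39, power 35%. For HR 2.0: √15 × ln 2 − 1.96 = 0.73, power 77%. For 80% power, 191 and 66 deaths are needed.
- The article reports 140 patients but not their split. If it were even (about 47 per group, at most about 93 deaths), the same formula gives about 50% for HR 1.5 and 92% for HR 2.0.

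**The case against.** The strongest reply has five parts.

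- **The model matches the wording.** The hypothesis speaks of risk, and cumulative risk is what a subdistribution model addresses. This stands to the extent that the subdistribution HR is a valid measure of absolute risk and should stay. It does not make it sufficient as the sole measure for whether salvaged blood promotes progression.
- **OS is part of the same hypothesis.** Excess SBT mortality would count against safety there, by log-rank test and adjusted Cox regression. This stands as a partial safeguard. Its power is low for moderate effects at the minimum group size. It also pools deaths before and after progression, so it cannot isolate the progression rate among patients alive and progression-free.
- **The curves would show early harm.** In the 0.04/0.04 setting above, progression with SBT against comparator is 13.2% against 10.7% at 3 months, 22.5% against 19.1% at 6 and 33.7% against 30.9% at 12. The curves cross at about 22 months. This stands for that setting, but the named effect measure is the single HR, and no curve for death without progression is planned.
- **Reversal needs strong conditions.** This stands. With rare competing death (0.05/0.01) it takes a death HR of about 2 to hide a progression HR of 1.3. If SBT does not affect death, the ratio is only mildly attenuated.
- **An analysis plan that is not shown may add cause-specific models.** It may. The article nevertheless fixes the subdistribution HR as the measure, and the point is about that choice.

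Two stronger readings are tempting. A reader might infer that the Limitations section concedes this bias. It says only that deaths before 4 years may lead to underreported progression, and nothing about death differing by transfusion type. A reader might also take the ratio of log(1 − incidence) at month 48 as the model's result, which gives 0.88 for 0.04/0.04 with HRs 1.3 and 1.6, and 0.75 with HRs 1.0 and 1.5. The fitted model averages over follow-up and gives 0.93 and 0.78, so the month-48 ratios overstate the effect.

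**Conclusion.** The point holds as a conditional one. If SBT patients die sooner without progression, the only planned regression measure for progression can attenuate, hide or reverse a true increase in the progression rate. For a true HR of 1.3 the assumed settings run from 1.23 (death unaffected) through 1.10 (rare competing death) to 0.93 and 0.79 (frequent and clearly higher competing death). With no effect on progression at all, a death HR of 1.5 can look like a 22% reduction.

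These figures rest on constant hazards, complete 48-month follow-up and rates that the documents do not supply. The documents do not show that SBT patients will die sooner, nor that the subdistribution model is invalid. The fault is its use as the sole association measure for a hypothesis of no increase. The change is worth making because the error would favor a finding of safety on a stated primary objective, and because it costs little.

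**What to change.** State that the hypothesis of no increase in progression is assessed by the cause-specific Cox HR for progression, with deaths without progression censored, reported crude and adjusted for confounders. Beside it, report the cause-specific HR for death without progression and a cumulative incidence curve for that event by group, so that a difference in competing death is visible. Keep the planned progression curves and the subdistribution HR, labelled as a description of absolute risk. Specify this before the progression results are examined.

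The cost is two more Cox models and one more set of curves, in the software already named and with no new data. The cause-specific HR is open to confounding in this nonrandomized design just as the subdistribution HR is, so it needs the same adjustment. It also does not translate directly into absolute risk, which is why the existing analysis should stay.
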